### PCV introduction

Children receive PCV based on which cluster they reside in. The detail schedule and time of the vaccination are shown in the
Table 2. PCV vaccination started one month after the catch-up vaccination campaign so that all the children under three years of age in the intervention arm communes will receive PCV vaccination. Only those who are known to have allergy to PCV10 will be excluded from the study. Based on census data, we estimated that the annual birth cohort of children in each commune will be about 250 and there will be a total of 6,000 children to be vaccinated per year across the 24 treatment communes. The corresponding number of vaccine doses required is 13,500 per year. Vietnam’s National Immunization Program (NIP) vaccinate DPT-HepB-Hib vaccine at two, three, four months and JE vaccine at 12 months. We will integrate PCV into the same visit as the above NIP vaccines to obtain optimal coverage.

**Table 2. T2:** Different PCV vaccination schedules and timing of the vaccination.

Schedule	0p+1	1p+1	2p+1	3p+0	Unvaccinated
**2 months**		X	X	X	
**3 months**				X	
**4 months**			X	X	
**12 months**	X	X	X		

### Cross-sectional carriage surveys

We will conduct cross-sectional nasopharyngeal carriage surveys before the catchup vaccination campaign (baseline carriage survey), four months after the second dose of catch-up vaccination (post-catchup carriage survey), and annually during the same month that the baseline survey was conducted in. In each carriage survey, 60 children four to 11 months old, 60 children 14 to 24 months old and their mothers (120) in each of the 27 study clusters will be enrolled and screened for the presence of vaccine-serotype carriage. The census database and regularly updated EPI vaccination list of children are used to randomly select study subjects. The data manager from NU will create a random list based on a list of eligible children using Stata software version 14. Informed consent will be obtained from mothers or guardians of the child before enrolment by medical doctors or health staff at commune health centers. The baseline carriage survey will reveal the background
*S. pneumoniae* carriage patterns while the second carriage survey after the catchup vaccination will reveal the effect of catchup vaccination and initial vaccine introduction in the community. The subsequent annual carriage surveys will reveal the
*S. pneumoniae* carriage pattern among clusters receiving different PCV vaccination schedules.

### Sample collection and testing

Nasopharyngeal samples will be collected from the study participants. The initial screening test will be conducted locally at the Pasteur Institute in Nha Trang. DNA will be extracted from the nasopharyngeal samples and screened for the
*S. pneumoniae* lytA gene using real-time PCR. The positive samples will be cultured, DNA extracted and then the DNA samples will be transported to MCRI for serotype determination by Microarray assay, the most sensitive of serotyping methods
^
20
^. All the data will be double-entered and checked before the data analysis. Data managers from NIHE and NU will manage the database, and only the data without personal information will be shared with other main investigators from the London School of Health and Tropical Medicine (LSHTM) and Murdoch Children's Research Institute (MCRI) for data analysis. In accordance with the ethical approval, the residual samples will be stored for five years after completion of the study for future confirmatory testing. Clinical trial insurance contract has been obtained to cover the AE, SAE treatment cost and compensatory payments.

### Patient and Public Involvement

The study subjects were less than 24 month-old children, eligible for routine vaccination in the community and they were not involved in the development of research question, outcome measures, the design of the study. Fieldworkers from the commune health centers conduct the home visit, explained the study and requested informed consent from the parents or guardian of the subjects to participate in the study. The results of the study will be shared with the local health authorities and the local health authorities will disseminate the study results to the parents and guardian of the participants. The parents or guardian of the children participating in the study were asked to report any discomfort or side effect of the PCV10 vaccination and nasopharyngeal sample collection during the carriage surveys. 

### Approach and data analysis

The comparison of carriage prevalence in the intervention (1p+1 or 0p+1) clusters and the gold standard (2p+1 or 3p+0) clusters respectively will allow age-group specific assessment of non-inferiority of the 1p+1 and 0p+1 schedules if compared with the 2p+1 or 3p+0 schedules respectively in regard to protection against vaccine type carriage. The data will be analysed single-blindedly through an intention-to-treat analysis as this yields the most conservative effect that could be observed in a real-world setting. An absolute difference in prevalence of <5% will be used as the non-inferiority margin (see sample size calculations). As the primary analysis we will use a Chi-squared test of a difference in two proportions to estimate the treatment effect (
*i.e.* the difference between 1p+1 and 2p+1 arm VT prevalence in infants) following the approach detailed in Hayes and Moulton
^
16
^ for trials with fewer than 15 clusters per arm. The upper limit of the two-sided 95% confidence interval of the treatment effect not exceeding the specified non-inferiority margin of 5% will indicate non-inferiority.

**
*Mathematical modelling analysis*.** We will use data collected on age-specific VT and NVT prevalence to fit a dynamic age-structured meta-population model of pneumococcal transmission to changes in pneumococcal carriage prevalence over the study period in the 27 study communes. We will model the transmission dynamics of each of the five trial arms separately whilst also allowing for some degree of population movement between the arms to reflect the general dynamic behavior of the population. Incorporating movement will account for the possibility of spill-over effects between the different arms of the trial. Parameter estimation will be performed using adaptive Markov Chain Monte Carlo; we will estimate nine key parameters within the model from the collected data. These will be: age-group specific transmission rate for three key age groups for VT and NVTs (six parameters), the level of protection within each arm given by 1p+0 and 1p+1 (two parameters) and the rate of waning for the protection given by the 1p+1 dosing schedule. Chain convergence will be assessed through the use of the Gelman-Rubin statistic and efficient exploration of the posterior sample space will be confirmed by calculating the effective sample size. The estimated model parameters will then be used to predict the impact of PCV in a scenario where PCV had been introduced using the 1p+1 or 0p+1 schedules in all 27 communes. We will also use this framework to infer the impact of continuation with a 1p+1 or 0p+1 schedules in other transmission settings where PCVs have been in use and where high quality allows model calibration (secondary objective 4).

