### Study design

We will conduct a Phase IV cluster randomized trial in the 27 communes of Nha Trang city. The four different PCV schedules (1p+1, 0p+1, 2p+1, and 3p+0) form four corresponding intervention arms completed by an informal, non-randomised control arm without PCV use (
Figure 1). The unit of randomization, the clusters, are Nha Trang’s communes. We chose the three clusters that were to remain unvaccinated and randomly allocated the remaining 24 communes into six clusters per intervention arm.

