### Cluster and sample size calculation

We assumed that (i) the baseline prevalence of carriage of PCV10 serotypes among infants in Nha Trang is 32.5% and varies between communes from 20% to 45% and (ii) that carriage prevalence is reduced to 5% through the catch-up campaign and kept at the same level through routine vaccination under a 2p+1 or 3p+0 schedule.

Nasopharyngeal samples will be collected before the start of PCV vaccination in the site and at 6, 12, 24, 36, 48 and 60 months thereafter from 60 subjects per age groups (4-11mth old children, 14-24mth old children and their mothers) for each of the 27 clusters; adding up to 6,480 swabs per cross-sectional study and 45,360 in total. We assume that 10% of swabs cannot be obtained or cannot be interpreted in the laboratory. We calculated the number of clusters required to test our non-inferiority hypothesis under a type I error probability of 5% and 80% power.

As detailed in Hayes and Moulton
^
16
^ we calculated that 5.37 clusters are required to detect an increase in VT carriage prevalence among children in the 1p+1 arm compared with the 2p+1 or 3p+0 arms of 5% or more. Hence, six clusters for each intervention arm were included.

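### The primary-analysis paragraph contradicts itself: it names a chi-squared test on two proportions, but cites a few-cluster approach and decides on a confidence limit that this test does not give

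*Protocol article*

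**What the plan says.** All references are to the protocol article.

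- **Unit of randomisation (Study design):** "The unit of randomization, the clusters, are Nha Trang’s communes". Each of the four vaccine arms has six communes.
- **Named method (Approach and data analysis):** "As the primary analysis we will use a Chi-squared test of a difference in two proportions to estimate the treatment effect".
- **Effect, same sentence:** for example "the difference between 1p+1 and 2p+1 arm VT prevalence in infants".
- **Qualifier, same sentence:** the analysis follows a cited methods reference "for trials with fewer than 15 clusters per arm".
- **Decision rule, same paragraph:** "The upper limit of the two-sided 95% confidence interval of the treatment effect not exceeding the specified non-inferiority margin of 5% will indicate non-inferiority". The margin is absolute: "An absolute difference in prevalence of <5% will be used as the non-inferiority margin".
- **Sample size (Cluster and sample size calculation):** the number of clusters is calculated "under a type I error probability of 5% and 80% power". Carriage "among infants in Nha Trang is 32.5% and varies between communes from 20% to 45" per cent before vaccination, and 5% is assumed under the standard schedules. Sixty children per age group are swabbed in each commune, with 10% of swabs lost.

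**The concern.** The paragraph names one method and then relies on features which that method lacks.

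- A standard chi-squared test of two proportions takes two pooled counts per arm. It does not use the communes, so a condition on the number of clusters per arm has nothing to act on.
- It returns a p-value for equality. The decision rule needs a difference and its upper confidence limit.

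Two analysts could both claim to have followed the text. One would build an interval on about 6 × 54 = 324 swabs per arm, the other on six commune prevalences per arm. Close to the margin they could reach opposite conclusions. The pooled interval is the narrower one if communes differ, and in a non-inferiority comparison a too-narrow interval makes it easier to pass a schedule that is truly worse by the margin. This sentence governs both primary objectives.

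**Working it through.** **1. Does the design itself allow for clustering?**

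Inputs: p0 = p1 = 0.05, d = 0.05, m = 60, 80% power. The between-commune coefficient of variation, k, comes from reading the 20% to 45% range as four standard deviations (an assumption): k = (0.25/4)/0.325 = 0.192.

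Formula: c = 1 + (z_α + z_β)² × [p0(1−p0)/m + p1(1−p1)/m + k²(p0² + p1²)] / d².

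With one-sided α = 5%, (1.645 + 0.842)² = 6.183. Then:

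- sampling terms: 2 × 0.0475/60 = 0.001583
- between-commune term: 0.192² × 0.005 = 0.000185
- c = 1 + 6.183 × 0.001768/0.0025 = **5.37**, the plan's own figure.

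Without the between-commune term, c = 1 + 6.183 × 0.001583/0.0025 = 4.92. The sample size therefore allows for variation between communes, and the named test does not.

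**2. What does a pooled-swab interval do at the margin?**

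Take a true difference of exactly 5 points (10% against 5%), six communes per arm, m = 54 (60 less 10%), k = 0.192.

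- Variance of the difference per commune pair, swabs independent: (0.0475 + 0.09)/54 = 0.002546.
- Added between-commune part: 0.192² × (0.0025 + 0.01) = 0.000462.
- Inflation: (0.002546 + 0.000462)/0.002546 = 1.18.
- Chance that the pooled upper limit falls below 5 points: Φ(−1.96/√1.18) = 3.6%.

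**3. Simulation.** Beta-distributed commune prevalences, binomial counts of 54, 200,000 or more trials per setting. Entries are false non-inferiority rates at the margin; nominal is 2.5%. Repeat runs agree to about 0.1 to 0.2 points.

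| k | Source of k | Pooled-swab 95% interval | Commune-level t interval, 10 df |
|---|---|---|---|
| 0 | no clustering, for reference | 2.9% | 2.7% |
| 0.192 | implied by the sample size | 4.0% | 2.9% |
| 0.3 | assumed | 5.6% | 3.1% |
| 0.4 | assumed | 7.8% | 3.4% |
| 0.5 | assumed | 10.3% | 3.8% |

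The first row shows that about 0.4 points of the pooled excess come from the normal approximation at low prevalence, not from clustering.

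**4. Price of the commune-level interval.** With both arms truly at 5% and k = 0.192, the mean half-width is 3.9 points, against 3.3 for the pooled interval. The chance of concluding non-inferiority is 71%, against 82%.

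**The case against.** The strongest reply is that the sentence must be read to its end. It defines the effect as a prevalence difference and ties the analysis to an approach for few clusters; the trial is sized in clusters; and the decision rule sets a confidence limit against the 5-point margin. An article may leave the construction of the interval to the full protocol or analysis plan.

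Much of this stands, and it rules out four stronger readings that a reader might infer:

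- **That the plan ignores clustering.** It does not: the qualifier and the reproduced 5.37 both show that clustering was considered.
- **That the wrong null is tested.** Equality is the null of the chi-squared test, but non-inferiority is not declared from its p-value. The confidence-limit rule addresses the right hypothesis.
- **That no estimate is defined.** The prevalence difference is defined; the named test simply does not deliver its interval.
- **That the error rate is above nominal as a matter of fact.** The excess arises only if swabs are pooled, and the qualifier points away from pooling.

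It is also fair to say that the excess is modest at the plan's own variation, that the commune-level interval too lies slightly above 2.5%, and that the larger coefficients appear nowhere in the documents. The contents of the cited reference cannot be checked here, so nothing in this point depends on what it prescribes.

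The reply does not remove the inconsistency. The article does not omit the primary method; it names one, and that method fits neither the qualifier nor the decision rule. Cluster-adjusted chi-squared statistics exist, but the text does not name one, and a test statistic alone would still not supply the interval.

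**Conclusion.** The point holds as an internal contradiction in how the primary analysis is specified. The conclusion about the wording needs no assumption.

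The size is conditional on the named test being taken literally, with a 95% interval on pooled swabs. False non-inferiority at the margin is then about 4.0%, against 2.9% for a commune-level t interval and a nominal 2.5%. This rests on 54 evaluable swabs per commune, true prevalences of 10% and 5%, and k = 0.192 from reading the stated range as four standard deviations. That range describes communes before vaccination at 32.5%; the article gives no reason why relative variation should be the same near 5%. If it is larger, at an assumed 0.3 to 0.5, the pooled rate is about 5.6% to 10.3%, against 3.1% to 3.8%. The direction favours the reduced schedule.

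**What to change.** Replace the chi-squared wording with:

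> The primary analysis computes VT prevalence in each commune, estimates the arm difference as the difference in mean commune prevalence, and takes its two-sided 95% CI from the t distribution with 10 df; non-inferiority is concluded if the upper limit does not exceed 5 percentage points.

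State that this applies to 1p+1 against 2p+1 and to 1p+1 against 3p+0. The 10 degrees of freedom are 6 + 6 − 2.

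The change needs one sentence and simple programming, and no new data. The interval becomes somewhat wider: a half-width of about 3.9 instead of 3.3 points when both arms are at 5% and k = 0.192. The probability of success is then about 71%, where the pooled interval would show 82%. That difference is the price of respecting the unit of randomisation, and should be acknowledged when the sentence is changed.

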### Hospital pneumonia surveillance and severe adverse events monitoring

To address exploratory objective 1 and 2, we will monitor the incidence of pneumonia in the study areas, as a continuation of an ongoing population-based pneumonia surveillance project that has been in place in the area since 2007
^
21
^. Nasopharyngeal swabs will be taken from children attending to Kanh Hoa Province General Hospital (KHGH), the only public hospital in Nha Trang, with signs of clinically or radiographically confirmed pneumonia and coming from the study areas as an additional means of monitoring vaccine-type carriage in the study areas. This will enable us to evaluate this strategy of sampling for monitoring potential re-emergence of VT carriage in communities using the reduced schedule approach.

### Safety monitoring

The trial meets the ethical and regulatory requirements to monitor serious adverse events (SAE) in line with standards of good clinical practice. A SAE was defined as any event requiring hospitalization or resulting in death. Using the ongoing surveillance for acute respiratory illnesses at KHGH, we will monitor SAE potentially related to PCV vaccination. Any SAE such as hospitalization or death of a child within one month after receiving PCV will be investigated for its association with PCV vaccination. This process is similarly conducted for routine EPI vaccines as well. The Community Health Centre (CHC), local polyclinics and the Preventive Medicine Department of Kanh Hoa Health service in Nha Trang will support and collaborate on PCV related SAE monitoring. These health care institutions are also involved in the SAE monitoring related to EPI vaccination program in Vietnam and the safety monitoring meetings will be conducted every three-to-four months. If dangerous SAE are reported, the safety monitoring team can instruct to stop the study and report to MOH.

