### Ethics approval and consent to participate

Ethical approval was obtained by Ministry of Health, Vietnam (4875/QD-BYT), and Nagasaki University (15120149).

**
*Strengths and limitations of this study.*
** This study is designed to address whether a reduced PCV dosing schedule of one primary and one booster (1p+1) can be applied in a population with herd immunity against vaccine type PCV.

This study includes a PCV catch-up vaccination followed by a cluster randomized trial with four PCV intervention arms (1p+1, 0p+1, 2p+1, 3p+0) and three unvaccinated clusters in a PCV naïve population.

The primary outcome is the non-inferiority of vaccine type pneumococcal carriage among children in 1p+1 arm cluster compared to WHO recommended 2p+1 and 3p+0 arms clusters.

Limitations of the study include limited power for secondary outcomes.

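### The SAE definition is limited to hospitalisation or death, which is narrower than the good clinical practice standard the protocol says it follows

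*Protocol article*

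**What the plan says.** All the operative text is in the Safety monitoring section of the protocol article.

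- **Standard claimed:** "The trial meets the ethical and regulatory requirements to monitor serious adverse events (SAE) in line with standards of good clinical practice".
- **Definition, in the next sentence:** "A SAE was defined as any event requiring hospitalization or resulting in death".
- **Detection:** "Using the ongoing surveillance for acute respiratory illnesses at KHGH, we will monitor SAE potentially related to PCV vaccination". Commune-level health centres, local polyclinics and the provincial preventive medicine department "will support and collaborate on PCV related SAE monitoring". The same bodies do this for the routine immunisation programme.
- **Causality review:** "Any SAE such as hospitalization or death of a child within one month after receiving PCV will be investigated" for a link to the vaccine.
- **Stopping:** if dangerous SAEs are reported, the safety team may halt the study and inform the ministry.

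Three other sections bear on the point. PCV introduction says "Only those who are known to have allergy to PCV10 will be excluded from the study", and the section on the catch-up campaign makes the same exclusion. Patient and Public Involvement says that parents or guardians were asked to report side effects of the vaccine. Sample collection and testing says that the trial insurance covers both AEs and SAEs, so adverse events short of an SAE are a recognised category.

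**The concern.** The article names a standard and then gives a definition with only two criteria. The standard, as generally understood, treats an event as serious if it is life-threatening, causes persistent or significant disability, prolongs a hospital stay, or is medically important, as well as when it leads to admission or death. Under the article's wording, seriousness depends on admission or death and not on how dangerous the event was.

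This matters because SAE status controls two safeguards, the causality investigation and the stopping provision. It also determines what will be counted when SAEs are reported. The gap touches the one vaccine risk the article screens for, allergy to PCV10: a severe allergic reaction can be life-threatening and still resolve without admission.

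**Working it through.** No arithmetic applies, because the point rests on the wording of a definition. The check is to read every section that mentions SAEs, side effects or exclusions, and then apply the stated rules to a test case.

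**Step 1: is the definition widened anywhere?** The sections read were Initial catch-up vaccination, PCV introduction, Sample collection and testing, Patient and Public Involvement, Hospital pneumonia surveillance, and Safety monitoring. None adds a life-threatening, disability, prolonged-stay or medically important criterion. The causality sentence uses looser wording ("Any SAE such as hospitalization or death of a child within one month after receiving PCV will be investigated"), but it follows the definition and names the same two outcomes.

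**Step 2: apply the rules to two children with the same reaction.** Suppose each has a life-threatening allergic reaction within a month of a dose and recovers. Child A is admitted; child B is not. The case is an illustration: the article does not say where reactions are treated.

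| Rule in the article | Child A (admitted) | Child B (not admitted) |
|---|---|---|
| Meets the SAE definition | yes | no |
| One-month causality investigation of SAEs | applies | not formally reached |
| Stop-and-report provision for dangerous SAEs | can apply | not formally reached |
| Parent report of a side effect | possible | possible |
| Exclusion for known PCV10 allergy | can apply at a later dose | can apply at a later dose |

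The two children differ only in admission, yet the first three rows differ. The last two rows do not depend on SAE status.

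**Step 3: can the effect be sized?** No. The article gives no rate of severe reactions and no proportion managed without admission. It does give doses: 6 communes per arm x 250 births x (1 + 2 + 3 + 3) doses = 13,500 per year, which reproduces the figure in PCV introduction. That is a count of exposures. It says nothing about how many events would be misclassified.

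**Step 4: does it reach the primary result?** No. The primary endpoint is vaccine-type carriage prevalence, and none of the listed objectives is an SAE rate or a safety comparison.

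**The case against.** **The standard is not reproduced.** The article never lists the seriousness criteria, so the mismatch relies on the generally known content of good clinical practice. This is a fair limit. But the article chose that benchmark itself ("monitor serious adverse events (SAE) in line with standards of good clinical practice"), so a reader is entitled to hold the definition against it.

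**It is a condensed article.** The full protocol may carry complete criteria. That would excuse silence, but the article is not silent: it states a definition. If the full protocol has a wider one, the article misreports it and the two still need reconciling. This lowers confidence about what sites actually did. It does not remove the point.

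**Requiring hospitalisation might mean needing it, whether or not the child was admitted.** This reading is possible, but the text does not say so, and staff could apply it differently.

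**Stronger readings are tempting, and the documents do not support them.**

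- *Such reactions would go wholly unseen.* Parents were asked to report side effects, and community health bodies support the monitoring alongside the hospital. The event loses SAE status and what follows from it, but not necessarily its record. The parent-reporting sentence does mention the carriage surveys, so how far it covers the time after each vaccination is not fully clear.
- *A child would be re-exposed without review.* Because this is a "three unvaccinated clusters in a PCV naïve population", few children could have a known allergy before a first dose. But a recognised reaction to that dose could make the allergy known, and the exclusion does not depend on SAE status.
- *The SAE count will certainly be too low.* It could be, but only if such events occurred, and the article gives no basis for saying how many did.

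**It is late to change.** By the Trial status section, vaccination began in early 2017 and the year 5 survey was moved to July 2022. A new definition cannot redo years of collection. This stands, and it shapes the remedy.

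**Conclusion.** The point holds as a mismatch between the stated definition and the standard invoked beside it. As written, a life-threatening, disabling or otherwise medically important event without admission or death is not an SAE, and the causality investigation and stop-and-report provision do not formally apply to it.

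The effect is confined to safety classification and reporting. Its size cannot be derived, and the carriage comparisons are untouched. The conclusion assumes that the sentence in the article is the rule the sites used, that requiring hospitalisation was applied as actual admission, and that good clinical practice carries its usual seriousness criteria. If the full protocol has the wider definition and sites followed it, what remains is a correction to the article's text.

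**What to change.** Reconcile the definition with the stated standard. To the two existing criteria, add events that are life-threatening, that cause persistent or significant disability, that prolong a hospital stay, or that are judged medically important. State that a severe allergic reaction is assessed against these criteria whether or not the child was admitted. Use the health-centre route already shared with the routine immunisation programme, so that no new system is needed.

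For data already collected, re-screen the reported side effects against the full criteria before any SAE results are reported, and send those that qualify for the same causality review as other SAEs. If the records do not allow this, state plainly in the report that SAEs were limited to hospitalisation and death, and do not describe the definition as meeting the wider standard.

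The cost is a revised definition in the protocol and on the SAE form, some review work on existing reports, and possibly a slightly higher SAE count. How much review is needed depends on how many side effects were recorded, which the article does not say.
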